## Abstract

**Background:**

In the United Kingdom (UK), there is an extensive market for the class 'A' drug heroin and many heroin users spend time in prison. People addicted to heroin often require prescribed medication when attempting to cease their drug use. The most commonly used detoxification agents in UK prisons are currently buprenorphine and methadone, both are recommended by national clinical guidelines. However, these agents have never been compared for opiate detoxification in the prison estate and there is a general paucity of research evaluating the most effective treatment for opiate detoxification in prisons. This study seeks to address this paucity by evaluating the most routinely used interventions amongst drug users within UK prisons.

**Methods/Design:**

This study uses randomised controlled trial methodology to compare the open use of buprenorphine and methadone for opiate detoxification, given in the context of routine care, within three UK prisons. Prisoners who are eligible and give informed consent will be entered into the trial. The primary outcome will be abstinence status eight days after detoxification, as determined by a urine test. Secondary outcomes will be recorded during the detoxification and then at one, three and six months post-detoxification.

**Trial registration:**

Current Controlled Trials ISRCTN58823759

## Background

In the United Kingdom (U.K), there is an extensive market for the sale of heroin, an illicit class 'A' drug. Precise figures of how many people use and are dependent on heroin are difficult to establish as there has never been a national prevalence survey [1]. However, a 2004 survey found that 67% of people receiving drug treatment (out of a population of 125 545) identified heroin as their main problem drug [2]. The link between crime and illicit drug use, specifically heroin use, is well recognised. In 2002, 63% of injecting drug users (IDUs) in contact with specialist drugs services in England and Wales reported having ever been in prison or a young offenders' institution [3]. Because of the drug's highly addictive properties, those addicted to illicit opiates such as heroin require medical help in reducing and stopping their use.

Previously, neither the evidence base [1] nor the UK national guidelines on the clinical management of drug misuse [4] stipulated a 'drug of choice' for opiate detoxification in the prison setting. In the absence of an established evidence base, a wide variety of agents have therefore been used, they include methadone, dihydrocodeine, buprenorphine, lofexidine and clonidine. Currently, methadone and buprenorphine are recommended by national clinical guidelines [5]. Prior to the mid 2000s, the most commonly used drug for opiate detoxification had been dihydrocodeine. Anecdotally, dihydrocodeine was used because of a reluctance to prescribe methadone following a small number of methadone related deaths in prisons. Dihydrocodeine is attractive to clinicians as it has a shorter half-life than methadone, and seems equally acceptable to users. There was a move away from prescribing dihydrocodeine because of its potential for diversion by prisoners into the prison shadow economy, buprenorphine has been increasingly prescribed. Buprenorphine – in the form of sub-lingual tablets – has the potential advantage of having a good safety profile, a higher rate of adherence and lower withdrawal severity when compared to methadone, lofexidine or clonidine [6-9]. Its introduction into the prison estate was in line with increasing prescribing in the community [10]. An evidence base exists in the community for the effectiveness of methadone in achieving detoxification [4]. In 2004, policy initiatives recommended increasing the provision of methadone programmes within the prison setting [11]. Consequently, methadone was re-introduced into the prison estate in accordance with current best practice guidelines for prescription and administration.

Despite the changes highlighted above regarding recommendations for first-line agents, few clinical trials conducted in the UK prison setting have evaluated medication for opiate detoxification. Whilst one study evaluated the withdrawal severity of methadone and lofexidine [12], the rates of completion were not sufficient to detect a statistically significant difference between the two medications. In 2004, the Leeds Evaluation of Efficacy of Detoxification Study (LEEDS) team conducted the first randomised controlled trial (RCT) comparing buprenorphine and dihydrocodeine for opiate detoxification in the community [13,14]. The research team then compared these two agents in a pilot trial in HMP (Her Majesty's Prison) Leeds [15], and recently submitted the results for publication. The LEEDS trial has since expanded to compare the open use of buprenorphine to methadone across healthcare in several prisons.

### Sample size

In the situation of helping people detoxify from heroin, even a small advantage for an intervention could represent a worthwhile benefit. Therefore LEEDS has been planned to detect even a 15% difference in the proportion of opiate-free patients within the detoxification period i.e. percentage already abstinence 35% in one group and 50% in the other group. LEEDS expects to recruit 340 participants. A sample size of 340 people would yield at least an 80% chance (1 - β error or power) of detecting an absolute difference of 15% between the proportion of opiate-free patients in each group, at a two sided 5% level of significance (α error).

### Eligibility

#### Inclusion criteria

1. Male or female

2. 18 – 65 years old

3. Using illicit opiates as confirmed by a urine test taken at first assessment

4. Expressing a wish to detoxify through the standard monitored process and remain abstinent from opiates

5. Willing to give informed consent after receiving the participant information booklet

6. Remaining in custody for at least 28 days

#### Exclusion criteria

1. Contraindications to methadone or buprenorphine

2. Co-existing acute medical conditions requiring emergency admission for hospital care thus precluding detoxification in the prison setting

3. Currently undergoing detoxification from other addictive drugs whereby concurrent detoxification from opiates would not be clinically indicated

4. Previously been randomised into this trial

### Interventions

The treatment option will be concealed from both the participant and clinician/drugs worker at time of assessment. Both parties will remain blind to the selected treatment option until the envelope is opened.

1. Methadone, given openly, in the context of the standard prison doctor and drugs worker support.

2. Buprenorphine, given openly, in the context of the standard prison doctor and drugs worker support.

The reducing regimen of both methadone and buprenorphine (over less than 20 days) will be at the discretion of the prescribing doctor. However, the dose should not exceed this standard regime (Table 1).

**Table 1 T1:** Detoxification schedules

**Day**	**Buprenorphine** **(mg)**	**Methadone** **(1 mg/1 ml mixture)**
1	8	30
2	8	30
3	8	30
4	8	30
5	8	30
6	6	25
7	6	25
8	4	22
9	4	22
10	4	20
11	3.6	20
12	3.6	18
13	3.2	16
14	2.8	14
15	2.4	12
16	2.0	10
17	1.6	8
18	1.2	6
19	0.8	4
20	0.4	2

### Consent

Consent for the participant to enter the trial is gained at first presentation to the prison doctor or drugs worker after confirmation of eligibility criteria. Written consent will be obtained after the participant has made an informed decision. Information will be provided to the participant using an information leaflet documenting the aims, objectives and necessity of the study. The study has been approved by the research ethics committee (MREC Northern and Yorkshire).

### Outcomes

#### Primary outcome

Abstinence from illicit opiates at eight days post detox as indicated by urine test. A person who does not finish the course of detoxification or refuses to give urine will be considered not abstinent. If participants are released before the date of the urine test then the primary outcome will be based on self report in the community. If self report date is unobtainable then they will be noted as "loss to follow up".

#### Secondary outcomes

During the period of detoxification

##### Leaving the study early

Perceived reasons for withdrawal are recorded.

##### Inappropriate use of prescribed medication

Examples of this include storing, trading, swapping or selling of prescribed medication.

###### Overdose, self harm or suicide attempt

##### Service related outcomes

In-patient stays in prison healthcare will be recorded as will visits to a doctor, nurse or drugs worker

At one-month, three-month and six-month post detoxification

##### Abstinence status

Abstinence ascertained via urine test if the participant is still in HMP Leeds, Durham or New Hall, or has been transferred to another prison. If the participant has been released into the community then local community drugs service records are accessed.

All other outcomes as detailed above if the participant is still in the prison environment in which they were randomised.

The project team recognise the difficulty in tracking people with drug problems who have subsequently been released from prison across this period, particularly through the experience of conducting our pilot trial [15].

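### After detoxification, overdose, self-harm and suicide attempts are sought only from participants still in the prison where they were randomised, although transferred and released participants are followed for abstinence

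*Protocol article*

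**What the plan says.** The protocol article lists "Overdose, self harm or suicide attempt" among the secondary outcomes recorded while detoxification is under way. A second set of assessments follows: "At one-month, three-month and six-month post detoxification".

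At those later visits the Abstinence status section uses two different follow-up rules:

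- **Abstinence.** A urine test is sought "if the participant is still in HMP Leeds, Durham or New Hall, or has been transferred to another prison". For those who have left custody: "If the participant has been released into the community then local community drugs service records are accessed".
- **Everything else.** "All other outcomes as detailed above if the participant is still in the prison environment in which they were randomised".

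The same section gives a partial reason: "The project team recognise the difficulty in tracking people with drug problems who have subsequently been released from prison across this period". The Data collection section adds that extra contact with participants is kept to a minimum. The Adverse events section relies on clinicians' entries in the records and on researchers based at the prisons. No section names another source for overdose, self-harm or suicide attempt once a participant has been moved or released.

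**The concern.** Still being in the original prison at one, three or six months is a status acquired after randomisation. Participants who meet that condition are not the groups that were randomised, and the number observed can only fall as people leave. Events in those who have left are not looked for at all.

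This is a stated data-collection rule and not a detail left to a fuller document. A later analysis plan cannot recover events that were never sought. The rule is also narrower than the access the trial already has: a prisoner who has been transferred may still give urine for the trial, yet their overdose or self-harm history is not collected at the same contact.

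The Discussion expects the results to influence prison healthcare policy and prescribing guidelines if one agent proves better. A low or equal count of events among those who stayed could be taken as reassurance about the whole post-detoxification period, which the data would not support.

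**Working it through.** **1. The two follow-up rules compared (Abstinence status section).**

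| Participant's location at the visit | Abstinence | Overdose, self-harm, suicide attempt |
|---|---|---|
| Prison of randomisation | Urine test | Collected |
| Another prison | Urine test | Not sought |
| Community | Drugs service records | Not sought |

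The phrase about the prison environment is slightly loose. Set against the earlier mention of transfer to another prison, it reads most naturally as the randomising prison. Release is excluded on any reading.

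**2. Does eligibility keep people in the original prison until the visits?**

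- Entry requires "Remaining in custody for at least 28 days".
- Detoxification is described as "over less than 20 days", while Table 1 runs to day 20.
- The primary urine test is eight days after detoxification. 20 + 8 = 28 days, which uses up the required custody.
- With a 20-day course, and months taken as 30, 91 and 182 days, the later visits fall at about 20 + 30 = day 50, 20 + 91 = day 111 and 20 + 182 = day 202.
- A shorter course does not help, because the first visit is still at least 30 days after the start. The Data collection section dates the visits from randomisation instead. That puts them at about days 30, 91 and 182, all beyond 28.

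The entry criteria therefore do not assure custody at any of these visits, let alone custody in the same prison. This does not show how many will have left, because the article gives no rate.

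**3. Planned numbers.** The Sample size section plans 340 for 35% against 50%, two-sided 5%, 80% power. The allocation ratio is not stated, so 1:1 is assumed. With pooled variance and no continuity correction:

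n per arm = [1.96 × √(2 × 0.425 × 0.575) + 0.842 × √(0.35 × 0.65 + 0.50 × 0.50)]² / 0.15² = 169.3, rounded up to 170, so 340 in total.

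The stated figure reproduces (power 80.2% at 170 per arm) and is not in dispute. It is needed here only for the denominator of 170.

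**4. Precision lost.** With zero events in n people, the exact one-sided 95% upper limit solves (1 − p)ⁿ = 0.05, so p = 1 − 0.05^(1/n).

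| Share still in the original prison (assumed) | n per arm | Upper limit |
|---|---|---|
| 100% | 170 | 1.7% |
| 60% | 0.60 × 170 = 102 | 2.9% |
| 30% | 0.30 × 170 = 51 | 5.7% |

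Outside that range, 80% remaining (136 per arm) gives 2.2% and 20% remaining (34 per arm) gives 8.4%. The 100% row is a best case that no follow-up would reach in full. These limits measure lost precision only. They do not measure selection.

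**The case against.** The strongest defence is that this is a disclosed, pragmatic choice. The authors cite tracking difficulty learned from their pilot and want little extra contact with participants. The outcomes are secondary, and overdose, self-harm and suicide attempt are recorded throughout detoxification without this restriction. Dummy tables exist for all secondary outcomes but are not reproduced, so denominators may be properly defined there.

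Much of this stands, and it limits the point to the period after detoxification. It does not explain why transferred prisoners who still give urine are dropped for these events, or why community records opened for abstinence are not read for them. Extracting from a source already in use needs no extra contact with the participant. Well-designed tables would make the shortfall visible but would not fill it.

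A reader might also infer two stronger things that the article does not support:

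- **That the safety comparison as a whole is biased.** Selection is possible because the subset is formed after randomisation, but nothing in the article suggests that the allocated drug affects release or transfer. If leaving is unrelated to arm, the comparison among stayers remains fair, though smaller and less general. Numerical examples in which a difference among leavers is hidden can be built, but every input would be invented.
- **That most participants will have left.** A 28-day minimum gives no release or transfer rate.

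**Conclusion.** The point holds for post-detoxification events only. At one, three and six months the plan does not seek overdose, self-harm or suicide attempts after transfer or release, and any comparison of these events rests on a subset defined after randomisation. Recording during detoxification, the primary outcome and the planned 340 are unaffected.

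The size and direction of any bias cannot be stated. The loss of precision can only be illustrated: an upper limit of 2.9-5.7% with no events seen, against 1.7% at best. That rests on 1:1 allocation and 30-60% remaining, both assumed. It is a secondary weakness, worth correcting because most of the access needed is already in the plan.

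**What to change.** Amend the Abstinence status section along these lines: *At one, three and six months, overdose, self-harm, suicide attempt and death will also be extracted from the receiving prison or the community drugs service record whenever that source is used to establish abstinence.* Keep the same-prison restriction for prison healthcare visits and in-patient stays.

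Report events per arm over participants with information, split by source (same prison, other prison, community), beside the number randomised and the number without information. Label the post-detoxification result as partial. Do not use all randomised as the only denominator, because that would count people with no information as event-free and lower the apparent rate.

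The cost is a few extra fields at contacts already planned and possibly a minor amendment to the information sheet. Coverage will stay incomplete. The article does not say whether community drugs service records hold these events, and ascertainment there may differ from prison clinical records. Recruitment began in January 2006 and collection is described as ongoing, so participants whose visits have already passed may not be covered.

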## Discussion

As with our pilot trial in HMP Leeds [15], the information which the LEEDS project team aim to gain from this current trial is twofold. Firstly, once data collection is complete, we hope to show either a statistically significant difference between the efficacy of the two detoxification agents or alternatively, that no statistically significant difference exists (shown by p = > 0.05). We expect that the results will influence national prison healthcare policy and prescribing guidelines if the trial demonstrates one detoxification agent is significantly more efficacious than another.

Information about the methodological practicalities of conducting a multi centre, randomised controlled trial in the prison setting will be valuable. The research team have previously described the practicalities of conducting a detoxification RCT in primary care [13,14]. To our knowledge, however, only one British prison RCT comparing detoxification agents exists [12] aside from our prison pilot trial [15]. Therefore, conducting this current trial will provide new knowledge about the feasibility, practicality and day to day groundwork and management involved in running a trial in multiple prisons. This information may be important for future research teams. If successful, the trial will demonstrate the feasibility of multi centre trials within this environment.

Guidelines for substance misuse treatment in prison are not grounded on an established evidence base as there are very few trials conducted in this setting. Consequently, the project team envisage that this trial will provide valuable data about the efficacy of two routinely used detoxification agents which have rarely been studied within the prison environment.

## Approvals process

The extensive process of obtaining all necessary approvals for this trial and the issues surrounding this have been fully discussed in Sheard et al (2006) [16]. Research Governance approval was granted by Bradford South and West Primary Care Trust (PCT) on 2^nd ^December 2004. Research Ethics approval was granted from Multi Centre Research Ethics Committee (MREC) Northern and Yorkshire on 5^th ^July 2005.

The approval of the sponsor was gained on 28^th ^June 2005. A Clinical Trials Authority Certificate was issued from the Medicines and Healthcare Products Regulatory Authority on 28^th ^September 2005. The International Standard Randomised Controlled Trials number was granted on 15^th ^September 2005 (but backdated to 16 August 2005). Research governance for HMP Durham as an additional centre was granted by County Durham Primary Care Trust on 23^rd ^October 2006.
